### **Classification of ADRs by Expectedness**

ADRs will be classified by the Sponsor as either expected or unexpected:

**Expected:** an ADR that is listed in the current edition of the Product Monograph.

**Unexpected:** an ADR that is not listed in the current edition of the Product Monograph, or that differs because of greater severity or greater specificity.

### **Outcome of AEs**

The outcome of all reported AEs has to be documented as follows:

1. Recovered, resolved
2. Recovering, resolving
3. Not recovered, not resolved (by Study Completion visit)
4. Recovered, resolved with sequelae
5. Fatal
6. Unknown

**NOTE:** A patient's **death** per se is not an event, but an outcome. The event which resulted in the patient's death will be fully documented and reported.

### **Action(s) taken**

AEs requiring action or therapy must be treated with recognized standards of medical care to protect the health and well-being of the patient. Appropriate resuscitation equipment and medicines must be available to ensure the best possible treatment in an emergency situation.

The action taken by the Investigator must be documented:

#### ***a) General actions taken in the event of an AE***

- None
- Medication (other than IMP) or other (e.g., physical) therapy started
- Test performed
- Other (to be specified)

#### ***b) IMP-related actions taken in the event of an AE***

- None
- Product withdrawn
- Dose reduced

The Investigator will follow up on each AE until it has resolved or until the medical condition of the patient has stabilized. Any relevant follow-up information will be reported to the Principal Investigator (Sponsor).

### **7.4.3 Serious Adverse Events (SAEs)**

A **serious AE (SAE)** is any untoward medical occurrence that at any dose:

- results in death,
- is life-threatening (see below),
- requires hospitalization or prolongation of existing hospitalization,
- results in persistent or significant disability/incapacity,
- is another important medical event.

In this study a number of SAEs are expected because of the nature of the surgery. These events will not be considered as SAEs in this study.

**NOTE:** The term ‘life-threatening’ refers to an event in which the patient was, in the view of the reporting Investigator, at immediate risk of death at the time of the event; it does not refer to an event which may hypothetically have caused death had it been more severe.

In deciding whether an AE/ADR is serious, medical judgment will be exercised. Thus, important AEs/ADRs that are not immediately life-threatening or do not result in death or hospitalization but may jeopardize the patient or may require intervention to prevent one of the other outcomes listed in the definitions above should also be considered serious.

In addition, although not classified under the seriousness criteria, all suspected transmissions of an infectious agent will be reported as an SAE. A suspected virus transmission means that virus antigen has been detected in the patient. A passive transmission of antibodies alone does not constitute a suspected virus transmission.

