Our results are similar to those from other studies. A recent systematic review only identified 4 small, non-randomized studies – including our own (59) – comparing perioperative PCCs to FP in cardiac surgery (60). The meta-analysis showed PCCs were associated with reduced risk of RBC transfusion (OR 2.22; 95%CI 1.45-3.40) and fewer units of RBCs transfused (OR 1.34; 95%CI 0.78-1.90). PCCs were not associated with increased hospital mortality (OR 0.94; 95%CI 0.59-1.49), stroke (OR 0.80; 95%CI 0.41-1.56) or AKI occurrence (OR 0.80; 95%CI 0.58-1.12), suggesting that PCCs are more effective than FP without decreasing safety. In one of the studies in the systematic review, Arnekian and colleagues (61) compared three groups of cardiac surgical patients: 24 who received only PCC, 26 who received only FP, and 27 who received both products. In an unadjusted analysis, they found that RBC transfusions occurred least frequently in the PCC group and most frequently in patients who received both products. However, given the small sample size and lack of risk-adjusted analysis, few conclusions can be drawn from this study. In another study that included only patients who underwent pulmonary endarterectomy with cardiopulmonary bypass (CPB), Ortmann and colleagues (62) compared transfusion requirements and outcomes between 55 patients who received only FP and 45 patients who received only PCC for management of post-CPB coagulopathic bleeding. In an unadjusted analysis, they found that the PCC group had lower blood loss than the FP group, but transfusion rates were similar. They conducted multivariable regression analysis for AEs and found no differences between the two groups. However, given its small sample size, limited generalizability, and lack of risk-adjustment for efficacy outcomes, this study should be interpreted with caution. In a larger study, Cappabianca and colleagues (63) used propensity scores to match 225 patients who received PCC (with or without FP) to 225 patients who received only FP for management of post-CPB coagulopathy. They found that RBC transfusion requirements were lower in the PCC group (84% versus 93%), as were multiple (more than two units) RBC transfusions (51% versus 70%) and number of units of RBCs transfused (3.4 versus 5.2 units). While there were no major between-group differences in adverse outcomes, in a regression analysis that incorporated the propensity score the authors noted an association between PCC use and acute kidney injury that led them to caution about this potential risk. Similarly, in a recent multi-centre observational study not included in the above systematic

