### 3.1.2 Safety Endpoints

All AEs and SAEs will be collected from beginning of surgery (defined as entry into OR) to POD-28.

SAEs will be collected individually and as a composite (death, myocardial infarction, stroke, acute liver injury, acute kidney injury and thromboembolic events).

Incidence of all transfusion reactions, including transfusion-associated circulatory overload (TACO) and transfusion-related acute lung injury (TRALI) as per the International Society of Blood Transfusion (ISBT) (16) imputability of 'possible' or higher will be compared.

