#### 7.4.4 SAE Reporting Timelines

All SAEs, whether or not they are suspected to be related to study treatment (Appendix 15.1), will be reported within 24 hours of recognition to the Sponsor by telephone, fax, or email:

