## 4.7 Safety

All safety analyses will be based on the ITT population. If the SAF population differs from the ITT population then only AE information will additionally be displayed for the SAF.

The analysis of safety will study the following primary endpoints:

1. All adverse events (AEs) and serious AEs (SAEs) collected from beginning of surgery to postoperative day 28.

|                           |                 |             |               |
|---------------------------|-----------------|-------------|---------------|
| Statistical Analysis Plan | Version 2.0     |             | Page 15 of 19 |
| Sponsor                   | [name] | Protocol No | FARES         |

- a. SAEs collected individually and as a composite (death, myocardial infarction, stroke, acute liver injury, acute kidney injury and thromboembolic events).
- b. Transfusion-Related Acute Lung Injury (TRALI) and Transfusion-Associated Circulatory Overload (TACO)

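### Protocol 7.4.3 strips SAE status from unspecified surgery-expected events, and so can be read to cover components of the protocol's own SAE composite

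*Combined protocol and SAP*

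**What the plan says.** Protocol 7.4.3 defines an SAE by the standard criteria, the first being that the event "results in death". It then makes an exception: "In this study a number of SAEs are expected because of the nature of the surgery. These events will not be considered as SAEs".

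The safety endpoints in protocol 3.1.2 carry no such exception. On collection: "All AEs and SAEs will be collected from beginning of surgery (defined as entry into OR) to POD-28". On the composite: "SAEs will be collected individually and as a composite (death, myocardial infarction, stroke, acute liver injury, acute kidney injury and thromboembolic events". SAP 4.7 repeats this among its primary safety endpoints: "SAEs collected individually and as a composite (death, myocardial infarction, stroke, acute liver injury, acute kidney injury and thromboembolic events".

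On reporting, protocol 7.4.4 says: "All SAEs, whether or not they are suspected to be related to study treatment (Appendix 15.1), will be reported within 24 hours". On death, protocol 7.4.2 (Outcome of AEs) says that it "per se is not an event, but an outcome", while both versions of the composite list death as a component.

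**The concern.** Each of the six components can follow cardiac surgery without any study product being at fault. If a site regards a postoperative MI or AKI as expected from the operation, 7.4.3 tells it not to treat the event as an SAE, while 3.1.2 and SAP 4.7 require it to be counted in a composite of SAEs. The plan does not say which text governs.

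These are the events on which the safety comparison turns. The Background section says PCC may carry more thrombotic and renal risk than plasma. Of one matched cohort it reports that "the authors noted an association between PCC use and acute kidney injury", and it describes a second matched study that also found more AKI with PCC. The same section cites a meta-analysis with no increase in AKI (OR 0.80, 95% CI 0.58 to 1.12), so the question is open. Section 1.2 gives early detection of safety problems and Phase 3 sample-size inputs as uses of this pilot. A composite whose membership depends on how one sentence is read serves neither well.

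**Working it through.** There is no figure to reproduce. The documents state no expected rate for the composite or its parts, and the sample size has no statistical basis (protocol 9.1). The check is a comparison of texts.

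**1. Is the exception bounded anywhere?** Three places could limit it.
- Protocol 7.4.2 defines expectedness, but only for adverse drug reactions, by reference to the Product Monograph. It does not cover events expected from surgery.
- The waivers in 7.4.4 cover elective or pre-planned operations and prolonged stays for non-medical reasons. No clinical complication is listed.
- Appendix 15.1 is a flow chart that is not reproduced in the available text. Its footnotes are, and they repeat the SAE definition with no exception.

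The readable text therefore sets no limit.

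**2. Which outputs need the serious label, and which do not?**

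| Output | Depends on the serious label? | Source |
|---|---|---|
| Six-part composite | Yes, as worded: introduced as SAEs | Protocol 3.1.2, SAP 4.7 |
| Serious-TEAE tables | Yes | Protocol 9.2.1, SAP 4.7.1 |
| Fatal-event listing | Yes: fatal SAEs | SAP 4.7.1 |
| 24-hour reporting to the sponsor | Yes | Protocol 7.4.4 |
| Expedited reporting | Yes: seriousness is one of two conditions | Appendix 15.1 footnotes |
| Adverse-event data where consent cannot be obtained | Yes: Grade 3 and 4 SAEs only | Protocol 9.2.1, Appendix 15.2, SAP 3.2 |
| All-AE collection to POD-28 | No | Protocol 3.1.2 |
| Thromboembolic events by MedDRA SMQ | No | Protocol 9.2.1 |
| Listings of MI, stroke, liver injury, AKI, TEE | No: listed by event type | SAP 4.7.1 |
| Number of deaths, risk ratio, Kaplan-Meier | No | Protocol 9.2.1, SAP 4.7.1 |

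**3. What follows for the composite?** It can be programmed in two ways: filter on the serious flag and then on event type, or take event type alone. The two agree only if every component event is flagged serious. Section 7.4.3 allows them to differ, and neither document chooses between them. Protocol 9.2.1 promises a frequency table of composite events without saying which version it holds.

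**4. Where is there no backup record?** In consented patients an event that loses the serious label remains in the AE data. Where consent cannot be obtained, the only clinical data kept are hemostatic therapy and Grade 3 and 4 SAEs. An event denied SAE status there leaves no adverse-event record.

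**5. Does another rule compound it?** Under Causality of AEs (7.4.2), the investigator first asks whether the surgical course explains the event and grades the relation to study product only if it does not. A single judgement that surgery was the cause can thus bear on both conditions for expedited reporting, seriousness and causality.

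**The case against.** The strongest reply is that the exception names no event, whereas the endpoint sections name all six components and say they are collected; specific text can be taken to govern a vague general sentence. A reader might infer that 7.4.3 takes death, MI, stroke, liver injury, AKI and thromboembolism out of the composite outright. The documents do not support that. The sentence speaks only of a number of SAEs, and extending it to any one component is a reading, though an open one.

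A reader might also infer that these events would go unreported. That too is unsupported for consented patients: all AEs are collected to POD-28, deaths are counted separately, thromboembolic events are found by SMQ, and the other components are listed by type. The IDSMC reviews accumulating safety and endpoint data (3.3.9), not only expedited reports.

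Three further points stand.
- Section 7.4.4 is not contradicted. It sets a timeline for whatever counts as an SAE, and 7.4.3 narrows what counts.
- The statement that death is an outcome is a recording convention. The next sentence requires the event that led to death to be fully documented.
- Randomization is stratified by centre and outcome assessors are blinded, so uneven labelling between sites should fall on both arms alike. Bias in the arm comparison is not shown.

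The reply does not supply a limit on the exception, and it does not reach the outputs that use the serious label.

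**Conclusion.** The point holds as a faulty rule with a bounded effect. An unlimited exception to the SAE definition conflicts with the SAE composite in 3.1.2 and SAP 4.7. It could lower the counts in the label-dependent outputs tabulated above, or make the two sites' counts differ. The likely harm is to the absolute composite rate, comparability between sites and prompt reporting, more than to the arm comparison.

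No size can be given. A reader might assume that 10–25% of patients have AKI and obtain 0.10 × 50 = 5 to 0.25 × 50 = 12.5 events per arm. That rate is not in the documents. The figure also requires every AKI to be serious, every one to be dropped, and none to occur in a patient with another component. Setting such a one-arm shift against the confidence interval for a difference between arms would mislead, because a shift common to both arms largely cancels.

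The conclusion assumes that the Appendix 15.1 flow chart contains no list of excepted events. If it does, the gap narrows to whether that list includes any of the six components.

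**What to change.** In protocol 7.4.3, delete the two sentences. If relief from reporting is needed, replace them with a named list of peri-operative events that are exempt from expedited reporting only and are still recorded and analysed as SAEs.

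In protocol 3.1.2 and SAP 4.7, state that the six components always count towards the composite, whatever their expectedness or serious flag, and that death enters through the mortality record. Define the composite by event type in SAP 6.1, so that only one version can be programmed.

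The cost is a protocol amendment, one derived variable and more SAE forms. SAP version 2.0 already follows the blinded data review meeting, so an amendment may come too late to change labels already assigned. The SAP statement still works if made before any unblinded analysis. A blinded listing of component-type AEs not flagged serious would show whether the exception was used. Neither step recovers events never recorded for patients whose consent could not be obtained.

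A laboratory-based derivation of AKI and liver injury from routine values is optional, as a sensitivity analysis. Those values exist only where usual care produced them and stop at POD-7, while the composite runs to POD-28, so missing data would need to be reported with it.

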#### 7.4.4 SAE Reporting Timelines

All SAEs, whether or not they are suspected to be related to study treatment (Appendix 15.1), will be reported within 24 hours of recognition to the Sponsor by telephone, fax, or email:

***24 hours emergency [contact]***

#### Waivers from the SAE Reporting Requirement

Waivers from the SAE reporting requirement include surgeries that are elective or were planned before study entry or prolongations of existing hospitalizations for economic or social, but not medical, reasons. Such surgeries or prolongations of hospitalizations should not be considered SAEs.

#### 7.4.5 Other Relevant Safety Information

**Pregnancies**

Patients who are known to be pregnant will not be included in the study. In patients of reproductive age, pregnancy is ruled out prior to the cardiac surgery as part of standard of care.

**Overdose, interaction and medication error**

The following safety relevant information should be reported as an AE or, if the reaction fulfills one of the criteria for seriousness, as an SAE.

***a) Drug overdose***

An overdose is a deliberate or inadvertent administration of a treatment at a dose higher than specified in the protocol and higher than the known therapeutic dose that is of clinical relevance. The reaction must be clearly identified as an overdose.

***b) Drug interaction***

A drug interaction is a situation in which a substance or medicinal product affects the activity of an IMP, i.e., increases or decreases its effects, or produces an effect that none of the products would exhibit on its own. The reaction must be clearly identified as a drug interaction.

***c) Medication error***

A medication error involves the inadvertent administration or unintended use of a medicinal product which may be caused by the naming, presentation of pharmaceutical form/packaging, or instructions for use/labeling. The reaction must be clearly identified as a medication error.

## **8 DATA HANDLING AND RECORD KEEPING**

### **8.1 Documentation of Data**

#### **8.1.1 Source Data and Records**

Source data are defined as all information related to clinical findings, observations, or other activities in the study, written down in original records or certified copies of original records, allowing reconstruction and evaluation of the clinical study.

The Investigator will maintain adequate source records (e.g., case histories or patient files for each patient enrolled). Source records should be preserved for 10 years, as required by local regulations.

For each patient enrolled, the Investigator will indicate in the source record(s) that the patient participates in this study.

For data capture, a validated Electronic Data Capture (EDC) system providing an electronic CRF (eCRF) application will be used.

All data entered in the eCRF must be supported by source data in the patient records.

The Investigator will permit study-related monitoring, audit(s), REB review(s), and regulatory inspection(s), by providing direct access to the source data/records.

The Investigator may authorize site staff (e.g., sub-investigators, clinical research coordinators/assistants, nurses) to enter study data into the eCRF. This must be documented in the Delegation of Authority Log signed by the Investigator.

#### **8.1.2 Case Report Forms**

Authorized study site staff (e.g., blood bank technologist, research coordinator/assistant) will be responsible for completing an eCRF record for each patient enrolled. All site personnel will be trained on completion of a patient's eCRF. The site is also provided with the approved eCRF Completion Guidelines which will assist in data entry and data issues/questions. Additional site training may be provided as refreshers throughout the study, if needed. All persons allowed to enter or to change eCRF data must be listed in the Delegation of Authority Log.

For each patient enrolled, an eCRF record will be completed within the EDC system and finally approved by the Investigator or an authorized sub-investigator.

Prior to operational use, the eCRF application will be validated. All site personnel will be trained on the EDC system and study specific eCRFs prior to receiving access to the live system for data entry.

#### **8.1.3 Data Validation Procedures**

Monitors will perform source data verification (SDV) as defined for the study and described in the study Monitoring Plan.

If any errors or discrepancies in the eCRFs are found during data entry or review, discrepancies will be generated programmatically within the EDC system, and ‘manual’ queries will be generated by either a monitor or Data Management.

Discrepancies and queries can only be corrected by the Investigator(s) or other authorized site personnel. An audit trail documents all changes to the data over the entire study period. If the reason for a change is not obvious, a comment must be supplied in the query’s response, stating the reason for the change, prior to closing. The study monitor should provide guidance to Investigator(s) and the Investigator(s)’ designated representatives on making such corrections.

Once queries have been resolved by the site staff, the resolutions are assessed by Data Management. If the query response provided confirms the data as correct, the discrepancy will be closed. If the response does not adequately address the question raised, a new query will be issued for further clarification.

Manual checks are performed and programs are run throughout the study until the data is clean and the database is ready for lock. All discrepancies will be resolved prior to database lock. There will be a final run of the programmed checks to ensure all discrepancies are closed out, SDV will be confirmed as complete by the monitor, and all eCRFs will be approved by the Investigator prior to database lock.

## **8.2 Information to Investigators**

A Product Monograph will be handed out to the Investigator before the start of the study. The Product Monograph contains all information in the Sponsor’s possession necessary for the Investigator to be fully and accurately informed about the safety of *Octaplex*.

The Product Monograph will be updated at regular intervals by Octapharma and whenever relevant new information concerning the IMP becomes available. This will be delivered by Octapharma to the Principal Investigator/Sponsor who will distribute to the approved study sites.

The Investigator will be informed about the methods for rating relevant study outcomes and for completing CRFs to reduce discrepancies between participating Investigator and study sites.

The Investigator will be kept informed of important data that relate to the safe use of the IMP as the study proceeds.

## **8.3 Responsibilities**

At each study site the Investigator is accountable for the conduct of the clinical study. Responsibilities may be delegated to appropriately qualified persons.

A Delegation of Authority Log will be filled in and signed by the Investigator. In accordance with this authority log, study site staff (e.g., sub-investigators, nurses) are authorized to perform tasks relating to the study.

